## Abstract

**Background:** Acute lower respiratory tract conditions are highly prevalent in paediatrics. Many of these conditions present as consolidations on imaging studies. One of the most common causes is bacterial pneumonia (BP), which requires an accurate diagnosis to implement the best treatment plan. Despite the fact that major guidelines constrain the use of invasive tests, chest X-ray (CXR) or blood tests are still routinely used for the diagnosis. In this regard, the introduction of lung ultrasound (LUS) signified an advancement in reducing the invasiveness of diagnosis. However, there are still situations where distinguishing between different aetiologies remains challenging, especially in the case of atelectasis. **Methods:** This is a prospective cohort study to assess the diagnostic accuracy of new non-invasive, quantifiable, and reproducible imaging biomarkers (lung elastance and microvascularization ratio) for differentiating BP from another major entity that causes the appearance of consolidation in imaging tests, atelectasis. It will be conducted at Sant Joan de Déu Hospital in Spain from June 2025 to June 2027. Firstly, imaging biomarkers will be measured in well-aerated lung tissue without consolidation to establish their values in healthy lung tissue, according to a predefined imaging acquisition protocol. Subsequently, the imaging biomarkers will be assessed in patients with confirmed lung consolidation by LUS (Group 1: BP; Group 2: atelectasis). **Results**: The study aims to determine whether there are statistically significant differences in the biomarker values in relation to the normal values and between the different etiological groups. **Conclusions**: The demonstration of the reliable diagnostic accuracy of these biomarkers could significantly reduce the need for invasive techniques and improve the therapeutic management of many patients with BP and other pulmonary conditions presenting with consolidation in imaging tests.

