#### 2.4.3. Superb Microvascular Imaging Acquisition

For the study of tissue microvascularization, the transducer will be kept perpendicular to the skin, using the same intercostal window without modifying the patient’s position. The microvascularization ratio measurement will be performed using SMI within the colored box previously defined for lung SWE measurement (Figure 4). The SMI Doppler mode will be activated, along with the ‘Vascular Index’ tool, selecting a velocity scale of 0.9 m/s. A rectangular ROI (15 × 10 mm) will be selected at a maximum depth of 5 cm. Microvascularization results will be expressed as a percentage.

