## 3. Limitations

One of the main limitations of this project is that it is a single-centre study. However, it is a tertiary paediatric hospital that handles a high volume of patients, making the sample potentially large and representative at the population level. A potential selection bias in Phase 1 may arise from evaluating imaging biomarkers in patients who present to the hospital for reasons unrelated to pulmonary consolidation. This could limit the generalization of normal value results to the general population. Another limitation of the study is the potential for artifacts in biomarker measurements due to the presence of air in non-consolidated pulmonary tissue. If this issue occurs, it cannot be addressed by adjustments to the biomarker acquisition technique and would affect Phase 1 of the study. In this phase, it may be concluded that SWE and SMI are not reliable pulmonary diagnostic tools in the absence of consolidation. This could serve as a key preliminary finding of the study. In contrast, in Phase 2, where consolidated (non-aerated) pulmonary tissue is being assessed, the presence of air is unlikely to cause measurement artifacts. Another relevant aspect is the potential inter-observer variability, although this is not included among the objectives of the ELASMIC study, and thus, imaging biomarkers will be acquired by a single examiner. However, given that the examiner is a highly qualified professional trained in LUS image acquisition, the study assumes minimal inter-observer variability (the differences in measurements taken by another observer are negligible and clinically insignificant) and minimal intra-observer variability (the differences in measurements taken by the same examiner are negligible and clinically insignificant). Another limitation, which also represents a strength due to its innovative potential, is the use of diagnostic techniques that are not conventionally employed for evaluating lung tissue. In this regard, significant differences in the manual pressure exerted by the operator with the transducer could modify the measured results. Therefore, it will be essential to apply minimal pressure and verify the stability of the color map prior to the acquisition of the biomarkers.

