**Figure 4 diagnostics-15-00910-f004:**
[figure not shown]
Presentation interface of the SMI mode on the Aplio A500 device (Canon™).

**Table 1 diagnostics-15-00910-t001:** Comparison of the characteristics of CXR, LUS, SWE, and SMI for the evaluation of pulmonary pathology.

	CXR	LUS	SWE	SMI
**Irradiation**	Yes	No	No	No
**Bedside**	No	Yes	Yes	Yes
**Reproducibility**	Not operator-dependent	Operator-dependent	Operator-dependent	Operator-dependent
**Quantitative data**	No	No	Yes	Yes
**Type of information it provides**	Anatomy overview and possible pulmonary pathologies	Pleural effusions, pneumothorax, or superficial lung consolidations	Elasticity of the lung tissue	Lung microvascularization, (perfusion and small blood vessels)

CXR: Chest X-Ray; LUS: Lung Ultrasound; SWE: Shear Wave Elastography; SMI: Superb Microvascular Imaging.

**Table 2 diagnostics-15-00910-t002:** Set of variables to be collected during the study.

	Variables
**Anthropometric and Demographic**	- Age - Sex - Weight - Ethnicity
**Clinical and analytical**	- Reason for admission to PICU (if admitted) - Heart rate, respiratory rate, blood pressure and oxygen transcutaneous saturation and pulmonary auscultation findings. - Presence of respiratory failure criteria. - PRISM-III. - Analytical parameters (leukocyte count, CRP, PCT). - Aetiological study in biological samples collected. - Antibiotic treatment received. - Final diagnosis
**Respiratory**	- Need and type of mechanical ventilation (invasive/non-invasive) - Duration of mechanical ventilation - Respiratory pattern (obstructive/restrictive) - Lung compliance and resistance values (if invasive ventilation) - Radiological findings (if CXR performed)
**Ultrasound**	- Presence of A and/or B lines. - Presence of lung sliding. - Presence and description of pulmonary consolidations. - Presence of air bronchogram (position/type). - Assessment of the pleural space (free/fluid occupancy). - Presence of pneumothorax.
**SWE**	- Lung elastance values (KPa and m/s) in liver, healthy lung and in pulmonary condensation - Quantification of microvascularization through SMI (ratio) in healthy lung and in lung consolidation.

PICU: Paediatric Intensive Care Unit; PRISM-III: Paediatric Risk of Mortality; CRP: C-reactive protein; PCT: procalcitonin; CXR: Chest X-ray; SWE: Shear Wave Elastography; SMI: Superb Microvascular Imaging.

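### Observer variability is assumed negligible because of one examiner's training, so transfer of the normal values and cut-off to other operators, and the description of the biomarkers as reproducible, are unsupported

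*Protocol article*

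**What the plan says.** Section 3 (Limitations) of the protocol article raises the issue and sets it aside: "Another relevant aspect is the potential inter-observer variability, although this is not included among the objectives of the ELASMIC study". For that reason, "imaging biomarkers will be acquired by a single examiner". It then draws an inference. The premise is "given that the examiner is a highly qualified professional trained in LUS image acquisition". From this it concludes that "the study assumes minimal inter-observer variability (the differences in measurements taken by another observer are negligible and clinically insignificant"), and likewise "minimal intra-observer variability (the differences in measurements taken by the same examiner are negligible and clinically insignificant").

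Other parts of the article bear on this:

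- **Table 1**, reproducibility row: SWE and SMI are both rated "operator-dependent".
- **Section 3**, further on: differences in the pressure the operator applies could change the result, so pressure must be kept minimal and the colour map checked for stability.
- **Section 2.4 and the Discussion**: standardised acquisition is said to reduce operator variability, not to remove it.
- **Abstract**: the study concerns "new non-invasive, quantifiable, and reproducible imaging biomarkers". The Introduction and Discussion use the same adjective.
- **Section 2.2**: the outcomes include normal values and a cut-off for telling the causes of consolidation apart.
- **Section 2.4.2**: several SWE readings are implied. The two with the lowest standard deviation that also meet the interquartile-range limit are averaged for analysis.
- **Section 2.4.3**: "The microvascularization ratio measurement will be performed using SMI within the colored box previously defined for lung SWE measurement". The number of SMI readings is not given.

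**The concern.** The article does more than leave observer variability to another document: it asserts a result about it. The skill of one person gives no information on what a second person would measure, and that person's own repeatability can be measured instead of assumed.

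The aims depend on this. The Discussion wants the study to update how consolidations are diagnosed, which requires normal values and a cut-off that hold for other operators. If operators differ systematically, a threshold set by one of them will not keep its sensitivity and specificity for another. If the single examiner's own readings vary, that noise enters the reference range and weakens the contrast between groups.

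**Working it through.** **1. The text side by side.** The premise is one examiner with training. The conclusion covers (a) other observers and (b) the same observer. For (a), the between-examiner variance cannot be estimated with one examiner, whatever the sample size. For (b), repeat readings could estimate the variance, but the article assumes it. Table 1 and the pressure caveat both point against (a).

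**2. The plan's own figure.** Section 2.7 gives 53 per group for a three-group ANOVA with effect size 0.25 and 80% power, and sets significance at 0.05. With Cohen's f = 0.25 the noncentrality is N × f² = 159 × 0.0625 = 9.94. The noncentral F distribution then gives power of 0.805 at 53 per group and 0.797 at 52. The figure reproduces. No reliability term enters it, so it neither supports nor refutes the assumption.

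**3. Illustration for (a): an operator shift.** Assumptions not in the article: normal values with equal SD in both groups, BP the higher, means d = 2 SD apart, the cut-off at the midpoint, and a second examiner who reads s SD higher throughout. Sensitivity = Φ(d/2 + s); specificity = Φ(d/2 − s).

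| Shift s | Sensitivity | Specificity |
|---|---|---|
| 0 | Φ(1.00) = 84% | Φ(1.00) = 84% |
| 0.25 | Φ(1.25) = 89% | Φ(0.75) = 77% |
| 0.5 | Φ(1.50) = 93% | Φ(0.50) = 69% |
| 1 | Φ(2.00) = 98% | Φ(0.00) = 50% |

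With d = 1 the pairs are 69%/69%, 77%/60%, 84%/50% and 93%/31%.

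**4. Illustration for (b): within-examiner error.** The article gives no intraclass correlation (ICC), so a range is assumed for the analysed value. Random error reduces f to 0.25 × √ICC, provided that 0.25 describes error-free values.

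| ICC | f | Power at 53 per group | n per group for 80% |
|---|---|---|---|
| 1.0 | 0.250 | 80.5% | 53 |
| 0.9 | 0.237 | 75.9% | 59 |
| 0.8 | 0.224 | 70.6% | 66 |
| 0.7 | 0.209 | 64.4% | 75 |
| 0.6 | 0.194 | 57.2% | 87 |
| 0.5 | 0.177 | 49.3% | 104 |

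If 0.25 already describes values as observed, with their error, none of this loss applies.

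**5. Repeat SMI readings.** A single reading with ICC 0.5 / 0.7 / 0.9 keeps √ICC = 71% / 84% / 95% of the error-free standardised difference. The mean of three has reliability 3·ICC/(1 + 2·ICC) = 0.75 / 0.875 / 0.964, and so keeps 87% / 94% / 98%. This requires independent errors. Readings in one window share position and may share pressure, so the gain could be smaller.

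**The case against.** The strongest reply is that the design already deals with operator effects. A technique can be operator-dependent in general and still be controlled by using one operator, and the article specifies controls: light pressure, fixed region-of-interest sizes, a common window and a stability check. The limitation is disclosed, and observer agreement is expressly not an objective. The assumption feeds no calculation in section 2.7. The lung ultrasound training may cover SWE and SMI as well, since section 2.4 integrates both into the lung ultrasound protocol.

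Most of this stands. It supports comparing groups within this study. It does not support the claim about another observer, which the controls cannot test and Table 1 contradicts.

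A reader might infer more than the article supports:

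- **That no cut-off can be obtained.** One can be estimated for this examiner and device; only its transfer is untested.
- **That the BP-versus-atelectasis comparison is invalid.** One examiner keeps between-operator noise out of it, and purely random within-examiner error lowers power without creating a false difference.
- **That reproducibility is a planned conclusion.** It is a description of the biomarkers and not among the outcomes in section 2.2.
- **That only one SMI reading is taken, or that unused SWE readings are deleted.** Section 2.4.3 gives no number, and section 2.4.2 says only which readings are analysed.

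**Conclusion.** The point holds in a limited form. The article asserts negligible inter-observer differences that a single-examiner study cannot show and that conflict with Table 1 and its own pressure caveat. It also assumes negligible intra-observer differences when SWE repeat readings could estimate them. The within-study comparison and a cut-off specific to this operator and device are unaffected. The extension to other operators, and the word reproducible, lack support.

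The size is unknown because the article gives no reliability figure. Under the assumed 2 SD separation, an operator shift of 0.25 to 0.5 SD would move a cut-off from 84%/84% sensitivity/specificity to between 89%/77% and 93%/69%. An ICC of 0.8 would reduce power from 80.5% to 70.6%, but only if 0.25 is an error-free effect. These figures show why the assumption needs evidence. They do not show that the study is underpowered or that such shifts occur.

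**What to change.** 1. Delete the statement in section 3 that inter- and intra-observer differences are negligible.
2. Record every SWE reading taken under section 2.4.2. Report within-session, within-examiner repeatability (within-subject SD or coefficient of variation, and ICC) from all of them. The two selected for lowest standard deviation may understate the variability. Within-session figures do not cover variation between sessions, and the report should say so.
3. State that the normal values and cut-off apply to a single operator and device, and that inter-observer reproducibility is untested.
4. Stop describing the biomarkers as reproducible in the Abstract, Introduction and Discussion.
5. Optionally, where time allows, take repeat SMI readings in the same window so that SMI repeatability can be estimated too. Any gain from averaging depends on an unknown ICC and on independent reading errors. A range built on averaged readings should be labelled as such.

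The cost is a few more database fields, one descriptive table and more cautious wording, plus a little scanning time if the optional step is taken. No second examiner and no extra patients are needed. The recording change should come early, because readings not recorded at the bedside may not be recoverable.

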## 4. Discussion

Pulmonary pathology is highly prevalent in paediatrics, especially in the PICU setting. The differential diagnosis between various pulmonary conditions, such as BP and atelectasis, is crucial to provide the best therapy approach for each patient, limiting antibiotic use to those who truly need it, thus preventing overexposure to antibiotics and the rise of antimicrobial resistance. Currently, the differential diagnosis requires invasive procedures such as analytical extractions and imaging tests like CXR, which involve a high radiation burden. In this regard, bedside LUS has been widely introduced into daily clinical practice in recent years, and our research group has published several studies on its application in paediatrics and its impact on the etiological approach and therapeutic decision-making. In the study by Haakma et al., conducted in an adult ICU, it was concluded that the presence of dynamic air bronchogram in LUS exhibited a sensitivity of 45% (95% CI, 31–60%) and a specificity of 99% (95% CI, 92–100%) for BP diagnosis, while the presence of Colour Doppler imaging demonstrated a sensitivity of 90% (95% CI, 79–97%) and a specificity of 68% (95% CI, 56–79%) [11]. Therefore, there remains an opportunity to improve the diagnosis of BP and other causes of pulmonary consolidation through quantifiable and non-invasive biomarkers.

In this context, through this study protocol, we propose the investigation of new quantifiable and reproducible imaging biomarkers that provide individualized results and can be obtained non-invasively, aiming to improve the quality of care with a gender perspective and focused on the well-being of the patient and their family. Specifically, we suggest studying lung elastance measured by SWE and microvascularization ratio measured by SMI. The incorporation of these new techniques would represent a significant change in the diagnostic approach for patients with BP and atelectasis [32,33,34].

ELASMIC aims to update and enhance current protocols for diagnosing BP and other pulmonary consolidations. Specifically, it seeks to reduce the reliance on CXR while maintaining the current role of LUS in detecting various pulmonary consolidations. Furthermore, SWE and SMI could play a crucial complementary role to LUS in characterizing these pulmonary consolidations and providing etiological guidance. To achieve this, it is essential to determine the normal values for lung elastance and microvascular patterns in healthy lung tissue. These baseline values will enable the assessment of non-invasive biomarkers in patients with lung consolidation, ultimately facilitating differentiation between various potential causes. Standardized image acquisition and biomarker measurement will help reduce operator-dependent variability. Despite the limitations mentioned, achieving the study’s objectives could significantly improve clinical management through a quantifiable and non-invasive approach. Moreover, it may optimize therapeutic strategies by reducing the use of empirical antibiotics in patients without bacterial infections, which could have a substantial positive impact on global health.

## Figures and Tables

**Figure 1 diagnostics-15-00910-f001:**
[figure not shown]
(**a**) BP as seen by LUS, showing a large consolidation with branched air bronchograms inside. (**b**) VP seen by LUS, showing coalescent B-lines diffusely along with small, multiple subpleural consolidations. (**c**) Atelectasis seen by LUS, showing a large area of consolidation with parallel air bronchograms (non-dynamic).

**Figure 2 diagnostics-15-00910-f002:**
[figure not shown]
ELASMIC study phases. PICU: Paediatric Intensive Care Unit; LUS: Lung Ultrasound; SWE: Shear Wave Elastography; SMI: Superb Microvascular Imaging; BP: Bacterial Pneumonia.

**Figure 3 diagnostics-15-00910-f003:**
[figure not shown]
The TwinView feature of the Aplio A500 device (Canon™) allows for the visualization of the elastance map (**left**) and the propagation map (**right**).

**Figure 4 diagnostics-15-00910-f004:**
[figure not shown]
Presentation interface of the SMI mode on the Aplio A500 device (Canon™).

**Table 1 diagnostics-15-00910-t001:** Comparison of the characteristics of CXR, LUS, SWE, and SMI for the evaluation of pulmonary pathology.

	CXR	LUS	SWE	SMI
**Irradiation**	Yes	No	No	No
**Bedside**	No	Yes	Yes	Yes
**Reproducibility**	Not operator-dependent	Operator-dependent	Operator-dependent	Operator-dependent
**Quantitative data**	No	No	Yes	Yes
**Type of information it provides**	Anatomy overview and possible pulmonary pathologies	Pleural effusions, pneumothorax, or superficial lung consolidations	Elasticity of the lung tissue	Lung microvascularization, (perfusion and small blood vessels)

CXR: Chest X-Ray; LUS: Lung Ultrasound; SWE: Shear Wave Elastography; SMI: Superb Microvascular Imaging.

**Table 2 diagnostics-15-00910-t002:** Set of variables to be collected during the study.

	Variables
**Anthropometric and Demographic**	- Age - Sex - Weight - Ethnicity
**Clinical and analytical**	- Reason for admission to PICU (if admitted) - Heart rate, respiratory rate, blood pressure and oxygen transcutaneous saturation and pulmonary auscultation findings. - Presence of respiratory failure criteria. - PRISM-III. - Analytical parameters (leukocyte count, CRP, PCT). - Aetiological study in biological samples collected. - Antibiotic treatment received. - Final diagnosis
**Respiratory**	- Need and type of mechanical ventilation (invasive/non-invasive) - Duration of mechanical ventilation - Respiratory pattern (obstructive/restrictive) - Lung compliance and resistance values (if invasive ventilation) - Radiological findings (if CXR performed)
**Ultrasound**	- Presence of A and/or B lines. - Presence of lung sliding. - Presence and description of pulmonary consolidations. - Presence of air bronchogram (position/type). - Assessment of the pleural space (free/fluid occupancy). - Presence of pneumothorax.
**SWE**	- Lung elastance values (KPa and m/s) in liver, healthy lung and in pulmonary condensation - Quantification of microvascularization through SMI (ratio) in healthy lung and in lung consolidation.

PICU: Paediatric Intensive Care Unit; PRISM-III: Paediatric Risk of Mortality; CRP: C-reactive protein; PCT: procalcitonin; CXR: Chest X-ray; SWE: Shear Wave Elastography; SMI: Superb Microvascular Imaging.

## Data Availability

The original contributions presented in this study are included in the article. Further inquiries can be directed to the corresponding author.
